## Abstract

**Introduction:**

Psychiatric disorders are diagnosed through observations of psychiatrists according to diagnostic criteria such as the DSM-5. Such observations, however, are mainly based on each psychiatrist's level of experience and often lack objectivity, potentially leading to disagreements among psychiatrists. In contrast, specific linguistic features can be observed in some psychiatric disorders, such as a loosening of associations in schizophrenia. Some studies explored biomarkers, but biomarkers have yet to be used in clinical practice.

**Aim:**

The purposes of this study are to create a large dataset of Japanese speech data labeled with detailed information on psychiatric disorders and neurocognitive disorders to quantify the linguistic features of those disorders using natural language processing and, finally, to develop objective and easy-to-use biomarkers for diagnosing and assessing the severity of them.

**Methods:**

This study will have a multi-center prospective design. The DSM-5 or ICD-11 criteria for major depressive disorder, bipolar disorder, schizophrenia, and anxiety disorder and for major and minor neurocognitive disorders will be regarded as the inclusion criteria for the psychiatric disorder samples. For the healthy subjects, the absence of a history of psychiatric disorders will be confirmed using the Mini-International Neuropsychiatric Interview (M.I.N.I.). The absence of current cognitive decline will be confirmed using the Mini-Mental State Examination (MMSE). A psychiatrist or psychologist will conduct 30-to-60-min interviews with each participant; these interviews will include free conversation, picture-description task, and story-telling task, all of which will be recorded using a microphone headset. In addition, the severity of disorders will be assessed using clinical rating scales. Data will be collected from each participant at least twice during the study period and up to a maximum of five times at an interval of at least one month.

**Discussion:**

This study is unique in its large sample size and the novelty of its method, and has potential for applications in many fields. We have some challenges regarding inter-rater reliability and the linguistic peculiarities of Japanese. As of September 2022, we have collected a total of >1000 records from >400 participants. To the best of our knowledge, this data sample is one of the largest in this field.

**Clinical Trial Registration:**

Identifier: UMIN000032141.

## Introduction

Psychiatric disorders have a large impact on humans and can reduce quality of life (QOL) because of a high incidence and long duration of illness (1–3). According to global burden of disease surveys conducted by the World Health Organization (WHO) and other organizations, psychiatric disorders, including depression, bipolar disorder, anxiety disorder, schizophrenia, and drug addiction, are the leading medical disorders in terms of years lived with disability (YLDs), accounting for 18.7% of the global YLD in 2019 (4).

Psychiatrists diagnose psychiatric disorders by conducting one-to-one conversations with each patient. Historically, heuristic studies such as linguistics and psychopathology have vigorously studied the thought and language of psychiatric disorders. Several linguistic features are known, such as a loosening of associations in schizophrenia, flight of ideas in mania, psychomotor inhibition in depression, and circumstantial and word recall disorder in dementia. Although there is a common understanding of these linguistic features among psychiatrists, the diagnosis and evaluation of the degree to which a patient deviates from the range of what is considered healthy depend heavily on each psychiatrist's sensitivity and experience. One of the reasons why evaluations remain subjective is that there is no means of quantifying psychiatric diseases to date. These subjective judgments can lead to various problems, such as diagnostic disagreements among psychiatrists, unclear criteria for initiating treatment, and difficulty providing a standardized education of resident doctors. Although the characteristics of the disease appear in each patient's words, it is sometimes difficult to diagnose atypical cases or cases with very severe symptoms, as it can be difficult to determine what symptoms are causing the difficulty in coherent speech.

The absence of objective methods to detect psychiatric diseases has prompted several research to investigate biomarkers. Biomarkers were often obtained from some large datasets of EEG (electroencephalography) (5–7), fMRI (functional magnetic resonance imaging) (8–10), genomes (11, 12). Furthermore, using data-driven methods, these datasets aid in the discovery of novel biotypes and the extraction of cross-diagnostic characteristics (13, 14). These have the ability to forecast the diagnosis and course of an illness as well as the creation of novel therapies. In addition to EEG, fMRI and genomes, linguistic and acoustic features can also be used for the detection of biomarkers.

In recent years, there has been an increase in the number of reported studies that have attempted to diagnose psychiatric disorders using natural language processing (NLP). Target disorders include schizophrenia (15–20), depression (21), bipolar affective disorder (22), obsessive-compulsive disorder (23), autism spectrum disorders (24), dementia (25, 26) and many others. Many studies have utilized a wide range of NLP techniques from the morphological and syntactic analysis (27) to novel approaches for representing textual information such as n-grams (28), word2Vec (29), ELMo (Embedding from Language Models) (30), and BERT (Bidirectional Encoder Representations from Transformers) (31). Some studies have supposed the unique models that could explain specific pathological features such as poverty of thoughts (32), loosening of associations (33), thought disorder in psychosis (34), etc. A few studies have comprehensively analyzed speech data using and comparing the techniques reported in previous studies (35, 36). For example, Corcoran et al. have utilized the part-of-speech tagging analyses (which measures syntactic complexity) and Latent Semantic Analysis (which measures semantic coherence) to verify the machine learning classifiers based on these NLP methods for predicting psychosis onset (35). Morgan et al. have compared the abilities of the 12 NLP measures to differentiate speech data from subjects at clinical high risk for psychosis, first-episode psychosis patients, and healthy controls (36). Those measures included the total number of words, the number of ambiguous pronouns, the semantic coherence using Latent Semantic Analysis, and some indicators calculated by the speech graphs [developed by Mota et al. (34)]. Although findings of very accurate illness onset prediction have been published (37), there are still many open challengers: the lack of large datasets, the extraction of numerous features that are straightforward and reliable for clinical application, the search for features that are applicable to a variety of diseases, and analyses of the correlation between the disease time course and disease severity.

The present study aims to create large datasets of the Japanese language with a great number of samples, types, and amount of utterances and look into ways to extract linguistic and audio indicators that can be used to differentiate between healthy-disease and disease-disease. Such datasets are limited at present (38). They could enable us to obtain reliable results and bring pioneering insights from NLP in the Japanese-speaking region. Notably, this study aims to target 300–500 participants and obtain 600–2,500 corpora; as such, it will be one of the largest participants' records among studies examining the diagnosis of major psychiatric disorders using NLP. This research also aims to deepen our understanding of the characteristics of psychiatric disorders and quantify them using NLP and machine learning so that the features of psychiatric disorders can be identified and quantified in the future. Such technology could eventually be used for early diagnosis and prevention.

## Methods

### Dataset creation

In this section, we are going to describe the methods to create large Japanese-language datasets of adult patients diagnosed with major psychiatric disorders (depression, bipolar disorder, schizophrenia, anxiety disorder (including obsessive-compulsive disorder), mild cognitive impairment, or dementia) and healthy controls. We do not plan to make the datasets openly available because the possibility of containing personal information cannot be ruled out. They will be available to our collaborators and researchers who use them for scientific purposes after completing the ethics application modification process.

#### Participants

This study is a multicenter, prospective, observational study. Subject recruitment was started in 2018 and is ongoing. Participants are being recruited at seven hospitals and three outpatient clinics in Japan. Patient recruitment is being conducted at the following locations and hospitals: Tokyo (Keio University Hospital, Tsurugaoka Garden Hospital, Oizumi Hospital, Komagino Hospital, Oizumi Mental Clinic, Asakadai Mental Clinic), Kanagawa (Nagatsuta Ikoinomori Clinic), Shiga (Biwako Hospital), Yamagata (Sato Hospital), and Fukushima (Asaka Hospital). Participants are inpatients or outpatients aged ≥20 years who meet the diagnostic criteria for depression, bipolar disorder, schizophrenia, anxiety disorder (including obsessive-compulsive disorder), mild cognitive impairment, or dementia according to the DSM-5 or ICD-11. Healthy volunteers will consist of healthy individuals with no history of psychiatric disorders who have volunteered to participate in the study after reading the research group's website and printed recruitment advertisements and who are at least 20 years old at the time of consent. Researchers will obtain written informed consent about participation in this study and data storage from all the participants. In cases where the patients are judged to be decisionally impaired, the patients' guardians will be asked to provide consent. Participants will be able to leave the study at any time. This study was approved by the Institutional Review Board of Keio University School of Medicine and the participating medical facilities.

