##### Demographic characteristics

Sex, age, diagnosis, diagnosis subtype, duration of illness, prescription, and complications will be collected from the medical records. We will also collect as much information as possible about their education, birthplace, outpatient or inpatient status, years of education, educational background, occupation, work status, employment status, income, marital status, number of years of married (or divorced or separated), number of children, number of people living together, etc. If some information is missing, the patients will be asked to provide the information.

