##### Conversation data

Up to a 60-min conversation with a participating psychiatrist or psychologist will be conducted. We will confirm that the participant speaks Japanese-language as the primary. A participating psychiatrist or psychologist will avoid including the participant's identifiers in the recorded part of the conversation as much as possible. The conversation consists of three parts: free conversation, picture-description task, and story-telling task. During free conversation, a participant speaks with a psychiatrist or psychologist about the course of the illness, the patient's current condition, daily life, sleep patterns, interests and hobbies, and comments on news, movies, stories, and pictures, etc. No strict structuring is performed. During picture-description task, participants are presented with three pictures: one depicting three children eating donuts used in Visual Perception Test for Agnosia (VPTA), one showing the waterside used in COGNISTAT and one representing the shore used in WAB. The patients are asked to explain them in as much detail as possible. Pictures are presented in the same order to all participants. In story-telling task, participants are asked to describe the story of Cinderella in as much detail as possible. For example, a psychologist or a psychiatrist asks them, “Please think about how you would explain the story to someone who does not know the story.” If the participant does not know the story of Cinderella, the famous Japanese folktale “Kaguya-Hime” is used instead. The picture-description task and story-telling task each take about 10 min. In all the conversations, an interviewer is required to ask questions using neutral words, not using emotional-valenced words, to make an interjection, and to dig into the participant's story. The interviewer and participant are asked to wear microphone headsets named PRO8HE (39) (its range of the frequency of sampling is from 200 to 18,000 Hz, and its sensitivity is −55dB.), and the conversation is audio-recorded in a consultation room or similar quiet environment.

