In this study, not only the collection of linguistic information associated with each disease but also the relationship between illness severity and linguistic information will be important. Therefore, we will follow the participants two to five times during the study period to interview the subjects at times when the severities of their symptoms differ (i.e., severe, moderate, mild, and during remittance). An interval of at least 1 month between the two assessments will be required. The same procedures described above will be conducted for the follow-up data collection.

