### Sample size

The results of a pilot study conducted on 30 participants prior to the main study showed that the combined NLP and machine learning had an accuracy of 72–80% for binary classification to differentiate between disease and healthy controls (based on a leave-one-out cross-validation). The demographic data in the pilot study are as follows. Age (years, mean ± SD): 56.8 ± 16.9, Gender (%male): 46.7, Diagnosis: 5 schizophrenia, 1 bipolar disorder, 4 depression, 5 anxiety disorder, 5 neurocognitive disorder, and 10 healthy controls.

Specifically, we used the part of speech information as well as feature vectors extracted from the data points using an NLP package called SpaCy as the input to train an XGBoost model for predicting the labels of the data points. We cross-validated the XGBoost model using leave-one-out cross-validation (LOOCV) where we would leave one data point as the test data and train an XGBoost model using the remaining data points. The process repeated for each data point and computed the accuracy of the LOOCV as the ratio of correctly predicted data points out of all of the data points. We further optimized the hyperparameters of the XGBoost model by choosing the set of parameters that has the highest LOOCV accuracy.

We constructed a learning curve to estimate the number of samples required to achieve a classification accuracy of 90%. Starting from a sample size of 15, we randomly sample 15 data points from the total of 30 data points and perform the LOOCV as described above, and repeat the random sampling of 15 data points 10 times, each time keeping track the optimal classification accuracy to get an idea of the distribution of the accuracy for 15 data points.

We then repeat the whole process at one-sample increments until we reach 29 samples. The resulting accuracies are then fitted to a linear model. Based on the parameters of the fitted linear model, we estimated the number of data points required to achieve an accuracy of 90%.

We calculated that a minimum of 50 samples would be required. In addition, considering the variability of the data over a wide range of age groups, severity of illness, and regional differences, it was estimated that about 10 times the number of samples would be necessary. Another means of approximating sample sizes for regression analysis is that the number of cases should be approximately 10 times the number of the independent variables used to obtain statistical confidence (48).

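### Differently recruited patients and controls are compared to judge whether a feature is pathological, and neither a larger sample nor cross-validation removes age and sex differences between them

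*Protocol article*

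**What the plan says.** **Recruitment (Participants).** Patients: "Participants are inpatients or outpatients aged ≥20 years who meet the diagnostic criteria for depression, bipolar disorder, schizophrenia, anxiety disorder" and the other listed diagnoses, at seven hospitals and three outpatient clinics in five prefectures. Controls: "Healthy volunteers will consist of healthy individuals with no history of psychiatric disorders who have volunteered to participate in the study". They are reached through a website and printed advertisements, and the same age floor of 20 applies to them. Under Table 1, controls are also screened with the M.I.N.I. and must score at least 27 on the MMSE.

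**Variables collected (Demographic characteristics).** "Sex, age, diagnosis, diagnosis subtype, duration of illness, prescription, and complications will be collected from the medical records". Years of education and other background items are collected as far as possible.

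**Group comparison (Data processing and annotation).** Linguistic features thought typical of a disorder are compared between patients and healthy subjects and between disease groups. The article calls this step necessary to verify each variable's pathological validity before machine learning. Voice inputs include fundamental frequency, three formants, cepstral peak prominence and MFCC.

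**Modelling (Machine learning).** Models are evaluated by cross-validation. Task 1 predicts presence of a disorder; Task 3 predicts improvement or deterioration since an earlier assessment.

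**Sample size.** The learning-curve minimum of 50 is multiplied by about ten, "considering the variability of the data over a wide range of age groups, severity of illness, and regional differences".

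**Follow-up (Clinical assessment).** "The same procedures described above will be conducted for the follow-up data collection". Table 1 schedules healthy volunteers for the same repeat conversations as patients.

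**The concern.** A between-group difference shows that a feature is pathological only if the groups are otherwise comparable, or if the comparison allows for what differs. Here the two groups reach the study by different routes, and nothing in the stated eligibility rules brings their age, sex or education together. The M.I.N.I. and MMSE are eligibility screens; they do not balance demographics. The patient group includes people with neurocognitive disorder (79 of the 363 patients reported to September 2022), so age may well track diagnosis.

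Followed as written, the validity check could pass a feature that only carries age or sex. Such a feature would enter the models and be reported as a marker of disease. Two features of the plan might seem to protect against this but do not: a larger sample makes a confounded difference more certain, and cross-validation draws training and test records from the same imbalanced groups.

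**Working it through.** **1. The plan's own figures.** Learning-curve route: 10 × 50 = 500. Regression rule: 10 × about 100 variables = about 1,000, the stated desired size. Both reproduce. The base figure of 50 cannot be rebuilt, because the coefficients of the linear fit are not given.

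**2. What the documents give on comparability.** Pilot age is 56.8 ± 16.9 years over all 30 participants (20 patients, 10 controls). No age or sex by group is given for the pilot or the main study, and no control count for 2022. The actual gap is therefore unknown, and a range is shown.

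**3. How well age alone separates the groups.** Assume normal ages with within-group SD 16.9 and a mean gap of d years. Then AUC = Φ(d / (16.9 × √2)).

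| Assumed gap d (years) | d / 16.9 | AUC of age alone |
|---|---|---|
| 5 | 0.296 | 0.583 |
| 10 | 0.592 | 0.662 |
| 15 | 0.888 | 0.735 |
| 20 | 1.183 | 0.799 |

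The sample size does not appear in the formula.

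**4. Sensitivity to the SD.** The 16.9 is a pooled SD and already contains any patient-control gap. With a 2:1 split, the between-group part of the variance is (2/3)(1/3)d². If the pooled SD is held at 16.9 (variance 285.6), the within-group SD is √(285.6 − (2/9)d²):

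- d = 10: √(285.6 − 22.2) = 16.2, AUC 0.668
- d = 20: √(285.6 − 88.9) = 14.0, AUC 0.843

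Using 16.9 as the within-group SD therefore slightly understates separation at these gaps.

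**5. What a larger sample does to the validity check.** Simulation with assumed inputs: 2:1 patients to controls, independent records, and a feature with no disease effect and a within-group correlation of 0.5 with age. The test is at 5%, with 1,000 runs per cell (500 at N = 1,000).

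| Gap | N | Unadjusted: significant | Age-adjusted: significant | Mean AUC of feature |
|---|---|---|---|---|
| 5 y | 50 | 8.8% | 5.3% | 0.545 |
| 5 y | 500 | 36.5% | 5.2% | 0.543 |
| 5 y | 1,000 | 59.0% | 3.4% | 0.542 |
| 10 y | 50 | 15.5% | 4.8% | 0.584 |
| 10 y | 500 | 87.2% | 5.0% | 0.582 |
| 10 y | 1,000 | 98.8% | 4.6% | 0.583 |

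The feature's AUC does not change with N; only the chance of declaring it significant does. The formula agrees: Φ(0.5 × 10 / (16.9 × √2)) = 0.583. Adjusting for age brings the rejection rate back to about 5%.

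**The case against.** The strongest reply is that much of this rests on silence. No section says the comparisons are unadjusted or the groups unmatched. Covariates, fold structure and sensitivity analyses are commonly left to a fuller protocol or analysis plan, and collecting age, sex and education makes adjustment possible. This stands: the point can say only that no matching or adjustment is stated. What remains is stated in the article itself: two recruitment routes, and a group difference used as the test of pathological validity.

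A reader might infer more, which the documents do not support:

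- **That the plan offers sample size as its control of confounding.** Sample size scales up a learning-curve figure because real data vary more than the pilot. It makes no claim about bias, and it does not mention sex or medication.
- **That age explains the pilot's 72–80% accuracy.** No group-wise ages are given. A very large gap also conflicts with the pilot: 34 years would leave a within-group SD of √(285.6 − 256.9), about 5 years. Nor can balanced accuracy be set against raw accuracy from a 2:1 sample.
- **That practice coincides with recovery in Task 3.** Visits are at least a month apart and aimed at times of differing severity, and the task covers deterioration as well as improvement. "Pictures are presented in the same order to all participants" is standardisation, not a fault. The healthy volunteers' repeat visits already supply a comparator.
- **That controls differ from patients by site.** Where volunteers are interviewed is not stated. Common tasks, one headset model and a quiet room limit site effects, though they do not remove them.

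Severity and item-score prediction, and discrimination between diseases, do not rest on the patient-volunteer contrast.

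**Conclusion.** The point holds in a limited form. Recruitment gives no assurance that patients and healthy volunteers are alike in age, sex or education, yet a between-group difference serves as the check of pathological validity on inputs that plausibly carry age and sex. Neither the larger sample nor cross-validation within it removes that bias. Its actual size cannot be computed. The illustrative AUCs of 0.58 to 0.80 for age alone rest on normal ages, a within-group SD of 16.9 years and assumed gaps of 5 to 20 years; the simulation rests further on an assumed feature-age correlation of 0.5 and independent records. That the planned analyses will in fact be unadjusted is not established. The change is worth making because it is cheap and uses variables already to be collected.

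**What to change.** **Data processing and annotation.** Adjust the between-group comparisons for age, sex and years of education (education as far as it is obtained), and base the validity check on the adjusted difference.

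**Machine learning.** In the same folds as each main model, fit a demographics-only model with age, sex, years of education, and site where both groups are represented. Report the language and voice model's gain over it. For Task 1, add an age- and sex-matched or weighted subset as a sensitivity analysis.

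**Task 3.** Include visit number and interval in the benchmark, and use the healthy volunteers' scheduled repeat visits to gauge any practice effect.

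**Medication.** Examine it only within or between patient groups, since healthy volunteers cannot serve as the comparison for psychiatric prescriptions.

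**Reporting.** Give age, sex and education by group.

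The cost is analysis time only, with no new data collection. The downsides are wider intervals in matched subsets and smaller claimed accuracy gains.
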